### Study procedure

The study will consist of seven appointments, five of which will take place in short succession with an additional two after 6 and 12 months (Fig. 1). We will first apply two baseline assessments (behavioural data followed by MRI data), two intervention sessions (i.e., the neurofeedback training), and one post-intervention (Fig. 1). We chose to split the two baseline assessments (i.e., behavioural data assessment and MR imaging) to avoid fatigue. All sessions will have approximately 1 week in-between and will last between 40 and 80 min. Six and 12 months after the post-intervention, we will apply follow-up assessments. Each of the assessments will be described in detail below, and an overview can be found in Table 1.

**Fig. 1 Fig1:**
[figure not shown]
Study procedure. We will include *n* = 84 participants (*n* = 42 healthy elderly volunteers and *n* = 42 patients with Mild Cognitive Impairment). They will receive fMRI neurofeedback twice (Intervention I and II), and behavioural and MRI data will be assessed before and after the intervention. The figure has been designed by the authors

**Table 1 Tab1:** Schedule of assessments conducted during the study

	Baseline I	Baseline II	Intervention I	Intervention II	Post-Intervention	Follow-up I	Follow-up II
Blood sample	X						X
*Questionnaires*							
Scale of Self-Efficacy	X						
Spontaneous use of Imagery	X						
Neo-Five Factor Inventory	X						
State-Trait Anxiety Inventory	X						
Profile of Mood States			X	X			
Positie and Negative Affect Schedule			X	X			
*Cognition*							
Montreal Cognitive Assessment^a^	X						
Cognitive Functions Dementia^b^	X						
Stroop	X						
Digit Span	X						
Verbal Learning and Memory Test		X	X	X	X	X	X
*MR Imaging*							
Structural MRI		X			X		X
Functional MRI		X			X		X
Neurofeedback			X	X			

^a^In healthy elderly volunteers

^b^In patients with Mild Cognitive Impairment

### Baseline behavioural assessment

At the first baseline assessment, we will acquire behavioural data (both with paper-and-pencil tasks and with Delta 1.4.2 on a tablet) as well as draw blood. We will start with drawing blood followed by cognitive screening with the MoCA in healthy volunteers or the Cognitive Functions Dementia battery (CFD) in patients with MCI due to AD. Although cognitive functions have already been evaluated during the diagnostic process in patients with MCI, we chose to apply another evaluation to account differences in time from diagnosis and study participation. Additionally, we will implement the Stroop task as well as the Digit Span task. After cognitive screening, we will employ several questionnaires, all of which have been validated in German: Spontaneous Use of Imagery Scale, Scale of Self-Efficacy, Neo Five-Factor Inventory, and State Trait Anxiety Inventory. The questionnaires will assess mental imagery, self-efficacy, personality traits, as well as anxiety all of which may influence the ability to regulate brain activity and/ or respond to feedback. Variables from the questionnaires will be used later for prediction analyses. We expect in particular that participants who score high on mental imagery as well as self-efficacy would benefit from the intervention. Likewise, those with high scores on openness and low scores on state/trait anxiety may be those who learn fast from feedback. Blood will be drawn to determine the apolipoprotein E (ApoE) genotype as well as the genetic variant of the brain derived neurotrophic factor (BDNF). The ApoE genotype seems to influence hippocampal activity [17, 18] and will, therefore, be included as a covariate in our statistical model. Likewise, we will include the BDNF genotype as it serves as a genetic modifier of brain plasticity and, thus, may influence the ability to learn from feedback. Finally, we will obtain Aβ42 as well as Aβ42/40 levels from blood using Simoa technology using methods established by the Neurochemistry Lab Amsterdam University Medical Centres [19]. Since hippocampal hyperactivity is particularly present in those with increased Aβ (and vice versa), the acquisition of Aβ is of specifal interest for this study.

### Baseline MRI

MRI data will be collected with a 32-channel head coil on a 3 Tesla Magnetom Prisma scanner (Siemens Medical Systems, Erlangen, Germany) at the Translational Imaging Center Bern. First, a T1-weighted structural image is obtained using a magnetization-prepared 2 rapid acquisition gradient echoes (MP2RAGE) sequence (176 slices, repetition time (TR) = 5000 ms, echo time (TE) = 2.98 ms, inversion time (TI) = 2500 ms, flip angle = 5°, matrix = 240 × 256, voxel size = 1 × 1 × 1 mm). Next, task-related blood oxygenation-level dependent data will be acquired using a T2*-weighted echo-planar imaging (EPI) sequence. One thousand eighty volumes will be collected during a pattern separation task (see below); each volume will consist of 56 slices with 2.5 mm thickness (flip angle = 30 °, TR = 1000 ms, TE = 37 ms, matrix size = 92 × 92, voxel size = 2.5 × 2.5 × 2.5 mm). Finally, non-hemodynamic resonant saturation effects will be assessed with a phase-cycled stimulus-induced rotary saturation approach [20]. A spin-lock radiofrequency pulse set to 120 Hz will be used to sensitize images to a frequency in the range of oscillating neuronal currents induced by epileptogenic tissue. Two T2*-weighted EPI sequences (300 volumes, slice thickness = 5 mm, skip = 10 mm, flip angle = 90 °, TR = 139.55 ms, TE = 29.12 ms, matrix size = 64 × 64, voxel size = 3.3 × 3.3 × 3.3 mm) will be acquired simultaneously. Later, T2* effects will be separated from rotary saturation effects by deconvolving spin-lock-off from spin-lock-on images.

### Pattern separation task

We chose to apply a pattern separation task, as hippocampal hyperactivity has been found particularly with this task in patients with MCI [7, 8]. The pattern separation task will be presented with PsychoPy (version 3.1 [21];). All participants will complete two runs of an explicit version of the task [22], during which coloured pictures of objects will be presented. These objects can be new (first presentations), repetitions of previously shown objects (repetitions), objects similar to those previously shown (lures), or new objects presented only once (foils; Fig. 2). Participants will need to categorize each object as either new, old, or similar. One run will include 200 stimuli, and each stimulus will be presented for 2 s with 0.5 s inter-stimulus interval. The 200 stimuli will include 40 foils, 40 repetitions, and 40 lures with an additional 40 of first presentations for repetitions and lures, respectively. The order of object presentation will be randomized for each participant. As in previous studies, the contrast of interest for the definition of baseline hippocampal activity will be lures > foils [7].

**Fig. 2 Fig2:**
[figure not shown]
Pattern separation task applied during fMRI. For each run, 200 different objects will be randomly presented for 2 s (0.5 s inter-stimulus interval). The participants will need to decide whether an object is new, old, or similar. The figure has been designed by the authors with stimuli illustrations from https://github.com/celstark/MST

### Neurofeedback setup

Approximately 1 week after baseline MRI, we will apply the neurofeedback training on 2 days with 1 week in-between. Each neurofeedback session will last about 60 min and will consist of five runs of training as well as two transfer runs (one prior to the feedback runs and another one directly following the feedback runs). The transfer run will assess the innate ability to regulate activity without feedback (first transfer run) or how much of the learned ability can be maintained without feedback (final transfer run). Each run (i.e., transfer or training) will consist of baseline blocks and regulation blocks (5:32 min in total) but only during training, feedback will be provided (Fig. 3). The feedback signal will be calculated with OpenNFT [23]. We will use the same EPI sequence as during baseline MRI. All DICOM images will be transferred directly from the imaging computer to a laptop running OpenNFT. OpenNFT will process these images in real-time (i.e., faster than image acquisition) and estimate whole-brain activation maps using an incremental general linear model (iGLM) algorithm. We will apply intermittent feedback (i.e., feedback presented after regulation as compared to during regulation), as this was shown to be more effective than continuous feedback in promoting self-modulation of brain activity [24]. The feedback signal will be estimated based on activity-levels in the respective region of interest (ROI) as the percent signal change (PSC) between baseline and regulation blocks. The PSC will be calculated as the average of the spatial-temporal data obtained from within the ROI. Further, OpenNFT will dynamically use the average of the highest and lowest activity time points of the acquired ROI data to estimate maximum and minimum limits of scaling used to calculate the final PSC value. The estimated feedback signal will be sent to the presentation computer and then presented to the participant using a thermometer icon (Fig. 3).

**Fig. 3 Fig3:**
[figure not shown]
Neurofeedback setup. **a** The participants will see a slightly adapted version of the pattern separation task while they will need to downregulate activity in one of two regions of interest. **b** The functional brain activity in this region of interest will be measured continuously and sent to the laptop containing OpenNFT. **c** These data will be processed in real-time to estimate the percent signal change in the region of interest, which will be sent to the presentation laptop. **d** The value of the percent signal change will then be presented to the participants with a dynamic thermometer that changes colour from red (indicating increased activity) to green (indicating decreased activity). The figure has been designed by the authors with stimuli illustrations from https://github.com/celstark/MST and icons from www.flaticon.com

ROIs will be defined based on individual anatomical masks created with the individual T1-weighted images collected during baseline MRI. We will apply FreeSurfer (Linux-centos, v6.0.0, [25] to create individual ROIs and then co-register them to the motion correction file used for online realignment of the OpenNFT pre-processing pipeline.

### Neurofeedback session

The neurofeedback task as well as the feedback will be presented with PsychoPy (version 3.1, [21]). For each session, we opted for a block design that includes four repetitions. During the baseline condition, participants will need to slowly count backwards from 100 for 30 s (Fig. 4). During the regulation condition, a slightly adapted version of the pattern separation task will be applied for 44 s. Again, the participants will be randomly presented with objects. These will include six foils, six lures and six first presentations of subsequent lures (i.e., 18 objects in total). Again, each object will be presented for 2 s with 0.5 s inter-stimulus interval (Fig. 4). In contrast to the fMRI task, however, the participants will not need to respond in any way to these images but rather try to downregulate activity. Previous research has shown that a response from participants is not required to induce hippocampal activity [26]. For the regulation of brain activity, we decided to use an implicit approach, which means that participants are told the goal would be to modify the thermometer icon until the green colour appears but we do not suggest explicit strategies for how to achieve this goal (i.e., they will need to try different mental strategies in order to find a strategy that works best for them [27, 28]. Feedback on the success of the regulation will be presented for 4 s. During the transfer runs, the participants will see a thermometer icon without feedback (Fig. 4).

**Fig. 4 Fig4:**
[figure not shown]
Neurofeedback session. Each run will include four repetitions of baseline and regulation blocks, as well as the feedback presented using a thermometer icon. The thermometer icon will be filled with colours ranging from red to green during training or will remain grey during transfer. TR: Repetition time (1 TR = 2 s). The figure has been designed by the authors with stimuli illustrations from https://github.com/celstark/MST

Following the neurofeedback session, we will perform behavioural testing outside the scanner using a word list learning task (i.e., the VLMT [29];) that also probes memory functions. Afterwards, we will conduct debriefing of mental strategies. At the beginning and at the end of each session, we will apply the Profile of mood states (POMS [30];) and the Positive and Negative Affect Schedule (PANAS [31];) to assess whether the change in mood due to neurofeedback is similar for the control group and the experimental group.

### Post-intervention MRI

Approximately 1 week after the two neurofeedback sessions, participants will undergo post-intervention MRI. They will complete the fMRI pattern separation task that they have completed during baseline MRI (with different objects). In addition, we will again collect non-hemodynamic resonant saturation effects [20].

### Follow-up assessments

Approximately 6 and 12 months after the intervention, we will implement follow-up assessments. At the 6-months follow-up, we will only acquire behavioural data with the VLMT. At 12-months follow-up, we will apply the VLMT, draw blood again to obtain amyloid levels, and apply structural as well as functional MRI. For the fMRI task, we will again examine pattern separation performance (with different objects). In addition, participants will be examined using the MoCA (in healthy controls) or the CFD (in patients with MCI) for a second time.

### Statistical analyses

The primary outcome is the change in hippocampal activity as assessed with a pattern separation task during fMRI before and after both neurofeedback sessions. For the determination of intervention effects on hippocampal activity, we will compute repeated measures ANOVA with intervention (experimental vs. control group) and group (healthy volunteers vs. patients with MCI due to AD) as between-subject factors. We will include the genetic variants of ApoE and BDNF as covariates. Next, we are planning to compute regression analyses since we hypothesize that the reduction of hippocampal activity will be associated with memory performance change in the pattern separation task and the VLMT. As exploratory analyses, we will investigate whether any variable predicts successful neurofeedback; we will calculate the association between Aβ levels in blood and hippocampal activity; and we will identify the most successful downregulation strategies. For the prediction of successful neurofeedback, we will apply machine learning methods (e.g., cross-validated non-linear multivariate classification) to obtain the most important features.

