### Sample size calculation

For the determination of sample size, we used G*power [32]. Since no study so far tried to downregulate hippocampal activity, we opted for the detection of at least a small effect (i.e., cohen’s *f* = 0.25). This would require an inclusion of *n* = 84 in total (that is, *n* = 21 in each group) for a repeated measures design with 4 groups and 4 measurements (i.e., baseline, post-intervention, follow-up 1, follow-up 2). We used the following criteria to calculate sample size: ANOVA with repeated measurements and between-within interactions, α err = 0.01, 1-β = 0.99, number of groups = 4, number of measurements = 4.

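### The planned repeated measures ANOVA tests the primary pre/post change without adjusting for baseline hippocampal activity; the test is valid but less precise than an analysis using the baseline scan as a covariate

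*Protocol article*

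**What the plan says.** The Statistical analyses section defines the outcome: "The primary outcome is the change in hippocampal activity as assessed with a pattern separation task during fMRI before and after both neurofeedback sessions". The model follows: "we will compute repeated measures ANOVA with intervention (experimental vs. control group) and group (healthy volunteers vs. patients with MCI due to AD", these two being the between-subject factors. The adjustment is then given: "We will include the genetic variants of ApoE and BDNF as covariates". No other covariate is named for this model.

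The Sample size calculation section shows how baseline is treated. It counts "4 measurements (i.e., baseline, post-intervention, follow-up 1, follow-up 2" as the repeated measurements, and its criteria are "ANOVA with repeated measurements and between-within interactions, α err = 0.01, 1-β = 0.99, number of groups = 4, number of measurements = 4". Baseline is therefore one of the outcome levels, and the planned test is a between-within interaction.

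Table 1 schedules functional MRI at Baseline II, post-intervention and the 12-month follow-up. On the 6-month visit, the Follow-up assessments section says: "At the 6-months follow-up, we will only acquire behavioural data with the VLMT".

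**The concern.** Entering baseline as an outcome level amounts to subtracting it with a fixed slope of 1. When baseline and post-intervention values correlate at less than 1 (with equal variances), the best slope is rho, not 1, and subtraction over-corrects. An arm that starts higher by chance then tends to show a larger fall through regression to the mean alone. Allocation is stratified by age, gender and diagnosis, not by baseline activity, so the design does not limit that imbalance directly.

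What is at stake is the width of the confidence interval and the power of the primary comparison. The baseline value that would recover the lost precision is already scheduled for every participant.

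**Working it through.** **Inputs.** N = 84 with 21 per cell, so 42 per intervention arm; f = 0.25; alpha 0.01; power 0.99; 4 groups; 4 measurements (all from Sample size calculation). The baseline-to-post correlation rho is not given and is assumed, with a range of 0.3 to 0.7. SD means the between-participant SD of activity at one time point, assumed equal before and after.

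**1. The plan's own figure.** For the between-within interaction, lambda = f²·N·m/(1−rho), with (k−1)(m−1) = 9 and (N−k)(m−1) = 240 degrees of freedom. At an assumed rho of 0.5 and sphericity, lambda = 0.0625 × 84 × 4/0.5 = 42 and power is 0.992. The smallest N divisible by 4 that reaches 0.99 is 84, so the figure reproduces. Other correlations do not give it: N is 116 at rho 0.3 and 52 at rho 0.7.

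**2. Identity of the tests.** With two time points, the intervention × time F is the F for the arm difference in change scores. A numerical check on simulated data gave F = 7.6249 on 80 df both ways.

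**3. Variance per participant.**
- Change score: 2(1−rho)·SD²
- ANCOVA on baseline: (1−rho²)·SD²
- Ratio: (1−rho²)/[2(1−rho)] = (1+rho)/2

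The gap between the two is 2(1−rho) − (1−rho²) = (1−rho)², which is the contribution of chance baseline imbalance. Lost precision and exposure to imbalance are thus one problem, not two.

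| rho | change | ANCOVA | ratio | N for ANCOVA to match 84 |
|---|---|---|---|---|
| 0.3 | 1.40 | 0.91 | 0.65 | 84 × 0.65 ≈ 55 |
| 0.5 | 1.00 | 0.75 | 0.75 | 84 × 0.75 = 63 |
| 0.7 | 0.60 | 0.51 | 0.85 | 84 × 0.85 ≈ 71 |

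Simulated standard errors at N = 84 (change, ANCOVA) agree: 0.254 and 0.208, 0.218 and 0.188, 0.169 and 0.158.

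**4. Power, two arms and two time points.** In this layout f = 0.25 corresponds to an arm difference of 1 SD. Setting 2f²N/(1−rho) equal to delta²N/[8(1−rho)] gives delta = 4f = 1. The noncentrality is 84/[8(1−rho)] for change, and that value times 2/(1+rho) for ANCOVA, with 82 and 81 df, alpha 0.01.

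| rho | noncentrality, change | noncentrality, ANCOVA | power, change | power, ANCOVA |
|---|---|---|---|---|
| 0.3 | 15.0 | 23.1 | 0.888 | 0.983 |
| 0.5 | 21.0 | 28.0 | 0.972 | 0.995 |
| 0.7 | 35.0 | 41.2 | 0.9994 | 0.9999 |

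**5. Sensitivity.** With f = 0.25 kept on four cells and two time points (3 df, rho 0.5), power goes from 0.906 to 0.976. For an assumed arm difference of 0.5 SD at rho 0.5, it goes from 0.37 to 0.51 at alpha 0.01 and from 0.62 to 0.74 at alpha 0.05.

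**The case against.** The strongest reply is that nothing here is an error. The outcome is defined as a change, the model tests a change, and under randomisation the test is unbiased and keeps its type I error. Chance imbalance is already counted in the change-score standard error. All of that stands. A reader might infer that the planned analysis is biased or invalid; the document does not support that.

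The size is also open to challenge. Rho is an assumption throughout, and at 0.7 the power gain for a 1 SD difference has no practical value. A reader might take 1 SD as the effect the trial was planned on. It is not: the plan's f = 0.25 belongs to an interaction of four groups by four measurements, and the conversion to 1 SD holds only for two arms and two time points. A reader might also recompute the gain within the 42 patients with MCI, where it would look larger. The plan fits one model to all participants and states no MCI-only test, so such figures would not describe a planned analysis. Likewise, the intervention × time contrast compares 42 with 42, so 21 per cell overstates the exposure to imbalance.

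Finally, the identity with a change-score test is exact only for two time points. If the 12-month scan is a third level, the omnibus interaction tests several contrasts jointly and (1+rho)/2 does not describe it directly. Each contrast against baseline is still a change score.

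What remains is that the article fixes the model and its covariates, and for the comparison that defines the primary outcome a more precise analysis of the same data is available.

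**Conclusion.** The point holds as a matter of efficiency. For the pre/post primary outcome, the stated model gives an unadjusted change-score test, whose variance exceeds that of the baseline-adjusted analysis for any rho below 1, apart from one lost degree of freedom. At assumed rho of 0.3, 0.5 and 0.7, adjustment removes 35%, 25% and 15% of the variance; at 0.9 it would remove 5%. At 0.5, the value that reproduces the stated sample size, the standard error falls by 13% (√0.75 = 0.866).

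The stated 99% power is not a reason to ignore this. It was computed for four measurements, whereas activity is scanned three times and the primary outcome uses two. These figures assume equal variances before and after, and the power figures also assume the arm differences stated. The direction of the result is firm; its size is not, because the document gives no rho.

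**What to change.** Make the primary analysis an ANCOVA of post-intervention hippocampal activity (lures > foils contrast) on baseline activity from the same contrast, intervention, diagnosis, intervention × diagnosis and the planned ApoE and BDNF covariates. Report the adjusted difference between intervention arms with its confidence interval.

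Alternatively, use a mixed model for the three scans, with the baseline mean constrained to be equal across the randomised arms within each diagnosis. This gives the 12-month scan a stated place in the analysis. If the ANCOVA is chosen, say separately how that scan will be analysed. The constraint should not extend across diagnosis, which is not randomised; for the same reason a baseline-adjusted diagnosis effect does not mean the same as a comparison of changes.

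No new data are needed, since baseline functional MRI is scheduled for everyone. The cost is a change of wording and one degree of freedom, plus a small mismatch: the analysis would no longer be the between-within interaction used to derive N = 84. The article should note this and state the correlation assumed.

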**Methods:**

In a single-blind parallel-group study, we will randomize *n* = 84 individuals (*n* = 42 patients with MCI, *n* = 42 healthy elderly volunteers) to one of two groups receiving feedback from either the hippocampus or a functionally independent region. Percent signal change of the hemodynamic response within the respective target region will be displayed to the participant with a thermometer icon. We hypothesize that only feedback from the hippocampus will decrease hippocampal hyperactivity during pattern separation and thereby improve memory performance.

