The current study aims to test whether real-time fMRI neurofeedback is capable of reducing hippocampal hyperactivity in patients with MCI and, in addition, whether the reduction of hyperactivity will be associated with an improvement in memory performance. Comparable to previous studies, we will deploy pattern separation tasks to assess hippocampal activity as well as memory performance (e.g., [7, 8]). As there is evidence for an association between Aβ and hippocampal hyperactivity [9], we will determine Aβ levels in blood. In addition, we will examine variables that may predict neurofeedback success and identify the most successful regulation strategies.

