### Screening assessment and group allocation

We will screen participants during a telephone call (and only invite them to participate in the study if deemed eligible). Those who will meet inclusion criteria will be randomly assigned to the experimental group or the control group. The experimental group will downregulate activity in the hippocampus; the control group will downregulate activity in the intraparietal sulcus, a region that plays a key role in spatial attention [15] but not in pattern separation or memory. The participants will not be informed which area they will need to regulate (i.e., from which area they will receive feedback). Thus, we will apply a single-blind, randomized, parallel-group design. Choosing an alternative region in a control group will ensure physiological specificity to ensure that only the regulation of hippocampal activity (and not the regulation of any other brain region) will lead to a reduction of hippocampal hyperactivity and, in consequence, to an improvement in memory performance [16]. Group allocation will be conducted by the Clinical Trials Unit Bern with computer-generated random numbers, stratified for age, gender, and group status (i.e., MCI or healthy volunteers).

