## Discussion

This study will examine whether real-time fMRI neurofeedback can reduce hippocampal hyperactivity and whether the reduction will lead to an improvement in memory performance. This will extend former research showing that a pharmacological reduction of excess hippocampal activity in patients with MCI led to better memory performance using a pattern separation task [7]. In contrast to medication, real-time fMRI neurofeedback comes with considerably fewer risks or side effects [33]. In addition, it may give patients a sense of empowerment as they themselves tone down hyperactivity without having to ‘depend on’ taking medication. So far, the assessment of the effectiveness of downregulating the hippocampus requires using a set-up including an MR scanner. This study may provide insight into strategies that participants have successfully used to regulate hippocampal activity. It would be such strategies that may be included in future cognitive intervention studies. Should our study be successful, we will test whether other participants could use such strategies for themselves or whether each person will need to develop their own strategy. In the context of clinical use, only a few training sessions may produce long lasting effects [34, 35].

One aspect that may likely influence our results is the type of control group [28]. We opted for an active control rather than no feedback or yoked feedback; that is, feedback is given on the activity of a control region. In our view, only the comparison with an active control group can confirm that the results are specific to feedback from hippocampal activity [16]. However, differences between groups might still be related to differences in the perceived difficulty to regulate. We will account for this by evaluating how difficult participants thought it was to regulate.

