Since we will gather blood samples to assess Aβ levels, we may also be able to replicate previous research in healthy elderly individuals, or patients with MCI, that reported higher levels of Aβ are associated with increased hippocampal activity [7, 9]. We will extend prior research by testing whether this association is also evident using blood-derived Aβ levels. In addition, blood samples will be used for the determination of the genetic variants of ApoE and BDNF. This will allow an exploration of the association of gene status with hippocampal hyperactivity, the ability to downregulate via neurofeedback, and the improvement in memory performance. Besides the primary goal of reducing hippocampal hyperactivity, we may also provide information as to whether successful neurofeedback can be predicted by variables extracted from questionnaires [27]. We expect that participants who score high on mental imagery as well as self-efficiency would benefit from the intervention. Likewise, those with high scores on openness and low scores on state/trait anxiety may be those who learn fast from feedback.

One limiting factor of our study might be the single-blind design. We will not inform the participants from which area they will receive feedback; yet, investigators will need to generate the ROI files and prepare the individual neurofeedback setup. Thus, they will not be blinded. In future studies, a double-blind protocol that could be implemented by separating investigators whot prepare the individual setup from investigators who instruct the participants would be desirable.

In sum, our study will provide insight into the efficacy of real-time fMRI neurofeedback to downregulate hippocampal hyperactivity in patients with MCI due to AD. It will further elucidate whether downregulation will lead to memory improvement. Data extracted from questionnaires may help to identify factors that predict successful neurofeedback.

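### The article claims that hippocampal feedback improves memory, but the only memory analysis it states is a non-randomised regression of memory change on activity change

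*Protocol article*

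**What the plan says.** **The memory claim.** The Methods paragraph of the Abstract hypothesises that "only feedback from the hippocampus will decrease hippocampal hyperactivity during pattern separation and thereby improve memory performance", and the Abstract's Discussion paragraph promises an answer in the same causal terms. Screening assessment and group allocation justifies the active control arm on the ground that only regulation of the hippocampus "will lead to a reduction of hippocampal hyperactivity and, in consequence, to an improvement in memory performance". The Discussion opens by asking "whether the reduction will lead to an improvement in memory performance" and closes with: "It will further elucidate whether downregulation will lead to memory improvement". The Background is the exception. It words the aim as "whether the reduction of hyperactivity will be associated with an improvement in memory performance".

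**The analyses.** Statistical analyses fixes the primary outcome: "The primary outcome is the change in hippocampal activity as assessed with a pattern separation task during fMRI". The randomised comparison is tied to that outcome: "For the determination of intervention effects on hippocampal activity, we will compute repeated measures ANOVA with intervention (experimental vs. control group"), with diagnosis group as the second between-subject factor. For memory the section turns to regression analyses, giving as the reason that "we hypothesize that the reduction of hippocampal activity will be associated with memory performance change in the pattern separation task and the VLMT". No section of the article states a comparison of memory between the two arms.

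**The concern.** The control arm exists so that a benefit can be attributed to regulating the hippocampus and not to training in general. That protection comes from randomisation, and it reaches memory only if memory is compared between arms.

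Regressing memory change on activity change asks something else: whether people whose activity fell more also gained more on memory. Neither variable is assigned by randomisation. Attention, practice or disease stage can move both, in either arm. For the pattern-separation score there is a further link, because performance and activity come from the same task in the same scan. The VLMT is a separate word-list test given outside the scanner, so it escapes that link but not confounding in general.

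At stake is the second half of the trial's main hypothesis. A reduction in activity by arm plus a significant regression would invite the conclusion that feedback improved memory, although no randomised test of memory had been made.

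**Working it through.** **1. The sample size.** Sample size calculation gives 84 (21 in each of 4 groups) with f = 0.25, alpha = 0.01, power 0.99, 4 groups (k) and 4 measurements (m). It gives no correlation between measurements, so ρ = 0.5 with sphericity is assumed. For a within-between interaction:

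- λ = f²·N·m/(1 − ρ) = 0.0625 × 84 × 4 / 0.5 = 42
- df₁ = (k − 1)(m − 1) = 9
- df₂ = (N − k)(m − 1) = 240
- power = 0.992, and N = 84 is reproduced.

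That section ties the effect size to downregulating hippocampal activity. It contains no calculation for memory.

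**2. How often the regression is significant with no arm effect on either variable.** Assume a correlation r between reduction in activity and gain in memory, in the hypothesised direction. The documents give no value of r. With n = 84, Fisher's z gives

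P(significant) ≈ Φ(atanh(r)·√(n − 3) − z), with √81 = 9 and z = 1.960 (alpha 0.05) or 2.576 (alpha 0.01).

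For r = 0.3: 0.3095 × 9 = 2.786. Then Φ(2.786 − 1.960) = Φ(0.826) = 0.80, and Φ(2.786 − 2.576) = Φ(0.210) = 0.58.

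| assumed r | alpha 0.05 | alpha 0.01 |
|---|---|---|
| 0.2 | 45% | 23% |
| 0.3 | 80% | 58% |
| 0.4 | 97% | 89% |

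A simulation (4,000 trials, 42 versus 42, alpha 0.05) agrees: 80% at r = 0.3 and 97% at r = 0.4. In the same simulated trials the arm comparison of memory was significant in 4.5% and 4.4%.

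**3. The case where the primary outcome succeeds.** Let the experimental arm reduce activity by an assumed 0.8 SD more than control, with no arm effect on memory and a within-arm correlation of 0.3. The pooled correlation becomes 0.3/√(1 + 0.8²/4) = 0.3/√1.16 = 0.279, and Fisher's z gives about 73%. The simulation gave 72%, with the arm comparison of memory at 5.0%. A positive primary result together with a positive regression can therefore occur when feedback does nothing for memory.

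**4. What an arm comparison could detect.** Equal allocation (42 versus 42, or 21 versus 21 within MCI) is inferred from 21 per group. No dropout is assumed, and units are SDs of memory change. The normal approximation for 80% power at alpha 0.05 is (1.960 + 0.842) × √(2/42) = 0.61 SD. The exact noncentral t gives:

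| comparison | alpha 0.05 | alpha 0.01 |
|---|---|---|
| all, 42 vs 42 | 0.62 SD | 0.76 SD |
| MCI only, 21 vs 21 | 0.89 SD | 1.10 SD |

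Power for a 0.5 SD difference with 42 versus 42 is 62% at alpha 0.05.

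**The case against.** - **Memory is not the primary outcome, and the Background words the aim as association, which the regression matches.** Both are true, and they limit the severity. They do not remove the mismatch with the Abstract, the rationale for the control arm and the Discussion, all of which are causal.
- **A journal article condenses the full protocol, and secondary analyses may be set out elsewhere.** This stands as a limit. A reader might infer that the trial plans no arm comparison of memory at all, but the document supports that only for this article. The point is still more than an omitted detail, because the article names a memory analysis and that analysis does not test its stated hypothesis.
- **The sample size uses four occasions including the 6-month visit, where Follow-up assessments collects only the VLMT, so an ANOVA on the VLMT may be intended.** This is a fair hint. But no such ANOVA is stated, and the same section refers to downregulating hippocampal activity.
- **The 80% is simply the power to detect a correlation that was assumed.** This is correct. A reader might take it for a rate of false claims of memory benefit. It is not: detecting a real association is no error for an association hypothesis. It misleads only when the association is read as an effect of the intervention. The sign matters too. Shared attention or fatigue could move activity and performance in the same direction, which would count against the hypothesis. The figure holds only for a correlation in the hypothesised direction.

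**Conclusion.** The point holds in a bounded form. As written in this article, the plan provides no randomised test of the claim that hippocampal feedback improves memory. Its only stated memory analysis can be significant when the intervention has no effect on memory: in about 80% of trials at an assumed correlation of 0.3 (45% at 0.2, 97% at 0.4; n = 84, alpha 0.05), against about 5% for an arm comparison. The argument rests on the structure of the analysis and does not depend on the particular correlation.

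Two stronger readings are tempting. One is that the trial's main result is compromised. It is not on this ground, because the primary outcome is hippocampal activity and it is compared between randomised arms. The other is that the regression should not be done. It answers the association question posed in the Background and is useful as mechanistic evidence.

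**What to change.** 1. State as a secondary analysis a between-arm comparison of pattern-separation performance and of the VLMT, with intervention, diagnosis group and their interaction, adjusted for baseline memory. Name one of the two as the key secondary measure.
2. Keep the change-on-change regression as supportive and mechanistic, with arm and diagnosis terms.
3. Reserve the statement that feedback improves memory for a positive arm comparison. If no such comparison is added, reword the Abstract, Screening assessment and group allocation, and the Discussion to association, as in the Background.
4. Report the arm difference with its confidence interval, since a non-significant result would not exclude a moderate effect.

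The cost is a change of wording and one model per memory measure. No new data are needed: Table 1 schedules the VLMT before and after the intervention, and the pattern-separation task is done at the baseline and post-intervention scans. The downside is the modest power shown above, especially within MCI. That is a reason to specify the comparison in advance and report it with its interval; it does not justify letting the regression stand in for it.
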